### Long-term model-based cost-effectiveness analysis

#### Populating model parameters

Table 2 provides a list of key model parameters and the source for initial values, that is, mean, SD or CI. To estimate all model initial values, we will use IPD from the I-WOTCH trial and GP records as well as any relevant publicly available evidence. Transitions from all model states to death will be extracted from age and sex adjusted all-cause mortality statistics from the ONS.^39^ Transition probabilities between all the other model states will be derived using risk equations from regression models (eg, time-to-event and/or logit-regression models depending on the nature of the transition). Costs and utilities parameters for each of the model states and events will be estimated using the regression models described in the Statistical analysis section. Variance–covariance matrices for each of the regressions will be extracted to inform the parameter uncertainty estimates in the model and used in the probabilistic sensitivity analysis (PSA) as explained in the Probabilistic sensitivity analyses section.

**Table 2 T2:** Model parameters to inform long-term decision analytic model

Transition probability	Sources	Specific details of the fields in source
Remaining in IT	NTP NCRF	Time of withdrawal from IT Time of withdrawal from IT
LTOT to IT	The trial	Proportion of people engaged in IT
IT to LTOT	NTP NCRF	Time of withdrawal from IT Time of withdrawal from IT
IT to SOLMP	NTP NCRF	Time of completely stopping the use of opioids Time of completely stopping the use of opioids
IT to dead state	PL	All-cause mortality data from ONS
Remaining in LTOT	The trial	Number of people who do not engage in IT and remain in LTOT
SOLMP to LTOT	PtQ GPRs	Medication data Prescription data
LTOT to PT	PtQ GPRs	Medication data Prescription data
LTOT to dead state	PL	All-cause mortality data from ONS
Remaining in PT	The trial PtQ GPRs	Number of people who remain in PT over time Medication data Prescription data
PT to LTOT	PtQ GPRs	Medication data Prescription data
PT to SOLMP	PtQ GPRs	Medication data Prescription data
PT to dead state	PL	All-cause mortality data from ONS
Remaining in SOLMP	PtQ GPRs	Medication data Prescription data
SOLMP to dead state		All-cause mortality rates from ONS
**Utility scores**	**Source**	**Specific details of the source**
LTOT	PL PtQ	Utility of opioid therapy^45^ Regression analysis of patient self-reported EQ-5D
PT	PtQ	Regression analysis of patient self-reported EQ-5D
IT	PtQ	Regression analysis of patient self-reported EQ-5D
SOLMP	PtQ	Regression analysis of patient self-reported EQ-5D
**Costs**	**Source**	**Specific details of the source**
LTOT	PL PtQ GPRs	Cost of opioid therapy per cycle^46^ Costs associated with self-reported resource use Costs associated with resource use collected
PT	The trial PtQ GPRs	Cost associated with usual care Costs associated with self-reported resource use Costs associated with resource use collected
IT	The trial	Cost associated with intervention
SOLMP	PL	Assumption—1× contact with GP^28^

‘The trial’ means the I-WOTCH trial.

GP, general practitioner; GPRs, GP records; IT, I-WOTCH tapering; I-WOTCH, Improving the Well-being of people with Opioid Treated CHronic pain; LTOT, long-term opioid therapy; NCRF, nurse clinical record form; NTP, nurse tapering plan; ONS, Office of National Statistics; PL, published literature; PT, patient-driven tapering; PtD, patient diary; PtQ, patient questionnaire; SOLMP, successful opioid-less management of pain.

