## Background

Nearly half of the UK adult population (43%) is living with chronic pain (ie, pain lasting >3 months), the prevalence of which increases with age.^1^ Opioids are commonly prescribed for chronic pain and a recent study reports an increase in the number of opioid prescriptions (approximately 34%) in England between 1998 and 2016.^2^ Analysis of prescription data shows that after this long increasing trend, there is a slight decrease in the annual number of opioid prescriptions for pain since 2016.^3^ Despite the demonstrated short-term effectiveness of opioids, evidence of their long-term impact in terms of pain relief and improvement in functional status is scant.^4 5^ This situation is compounded by concerns over the fact that long-term use of opioids can lead to adverse events (at an estimated absolute rate of 78% in trials using a placebo as a comparator) affecting the respiratory, cardiovascular, gastrointestinal and central nervous systems.^6^ These include common adverse events such as dry mouth, nausea and constipation, as well as more serious adverse events including sleep-disordered breathing, respiratory depression and opioid-related deaths (at an absolute rate of 7.5%).^6–8^ Equally concerning is the fact that opioid use is associated with mental health and anxiety disorders, major depression and dysthymia.^9^ Their long-term use may cause problematic patterns of substance use, leading to substance use disorders (ie, abuse and dependence).^10^ Risk factors for opioid-related adverse events include older age, higher doses of this class of drugs and their long-term use.^11 12^

Clinical guidelines for prescribing opioids in chronic pain recommend tapering when the possible harms from their use outweigh any expected benefits^13^ and yet, to our knowledge, no validated protocol or intervention exists to help patients reduce their opioid doses and manage their chronic pain.^14^ A number of studies have evaluated interventions (eg, acupuncture, ketamine-assisted dose reduction and behavioural strategies such as motivational interviewing, psychiatric consultation, cognitive behavioural therapy and mindfulness) that support opioid tapering.^15–18^ The conclusions drawn by these studies are limited by the quality of their design or insufficient follow-up period.^14^ Relevant for our study, there are no existing economic evaluations of opioid-tapering strategies in the management of chronic non-malignant pain.

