The EQ-5D-5L Questionnaire^23^ describes health in five domains (mobility, self-care, usual activities, pain or discomfort, and anxiety or depression). Each domain has five levels of severity (1—no problems/2—slight problems/3—moderate problems/4—severe problems/5—unable to do). A response consists of a sequence of five digits, for example, 12315, 12112, which represent the level of severity on each domain reported by the respondent. Combinations of the levels of the five domains describe 3125 possible health states. Several valuation studies have been carried out in the literature to estimate value sets for a given country/region. These studies used methods consistent with economic theory to elicit the respondent’s preferences towards the health states defined by the EQ-5D. A value set to calculate utility values for the EQ-5D-5L has been published recently^25^ but is still subject to methodological controversy. Until the controversies are resolved, we will convert EQ-5D-5L responses onto the EQ-5D-3L scale using the mapping function developed by van Hout *et al*
26 following current NICE’s recommendation.^24^

The CEA will integrate predicted survival and EQ-5D index scores (for each model state and clinical event) to derive an estimate of quality-adjusted life years (QALYs)—the health benefit of choice in our CEA—under the I-WOTCH and best usual care strategies.

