**Figure 1 F1:**
[figure not shown]
Simplified model structure showing patient flow during the I-WOTCH trial. At any time, individuals will be allocated to any five health states (shown as ovals). Individuals start in the long-term opioid therapy (LTOT) health state. Depending on the trial arm, they will move to either I-WOTCH tapering (IT) or patient-driven tapering (PT). The transition from LTOT to IT occurs only at the start of the trial and patients cannot go back to IT once they withdraw from it. Patients who have tapered their opioid doses completely will be in the successful opioid-less management of pain (SOLMP) health state. Patients may withdraw from IT or PT to move to LTOT health state. Similarly, patients in SOLMP may move to LTOT if they restart their opioid doses. The arrows‘ spearheads indicate the direction of allowed transition from one state to the other. Dead (D) state is an absorbing state where no transitions from the D state are allowed.

Each state is associated with an average cost and utility score, derived using the methods described in the Statistical analysis section. Spearheads of arrows in figure 1 represent the directions of allowed transitions per cycle. LTOT is the starting state for all patients in the I-WOTCH trial. Individuals in LTOT can engage with IT only once but are able to initiate PT at their will. While they remain in the LTOT state, individuals can experience opioid-related transient/emergent adverse events or persistent/serious adverse events. Occasionally, adverse events may trigger a transition from LTOT to PT. Individuals in IT or PT may withdraw from opioid tapering at any point in time and go back to LTOT. Individuals in IT or PT can transit to SOLMP state only when they are no longer taking any opioids. Finally, individuals are at risk of death at any point in time (ie, transitions into the absorbing D state are allowed from the LTOT, IT, PT and SOLMP states). A paper providing a detailed description of the conceptualisation of the model, health states definition, clinical events and associated transitions is in preparation. To maximise the use of the data collected during the trial and to model the events and transitions observed during the treatment and follow-up period, the state transition model uses a weekly cycle length during the first 4 months and monthly cycles beyond that.

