### Strengths

This paper describes the first economic evaluation analysis of a complex intervention to support opioid tapering, which uses data collected alongside the first UK-based RCT. A within-trial CCA will allow estimating relevant model parameters. The long-term impact on costs and health benefits from implementing the I-WOTCH Programme in England will be assessed in a lifetime decision analytic model populated using trial and previously published data. This analysis is based on a robust conceptual model that reflects clinical practice and long-term adverse events associated with both opioid use and opioid withdrawal. This model will enable estimation of I-WOTCH’s cost-effectiveness over a lifetime horizon and real-life subgroup analyses.

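### One ONS mortality schedule for every living state fixes the survival difference between arms at zero, and no planned analysis varies it

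*Protocol article*

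**What the plan says.** The mortality rule is explicit. Under Populating model parameters: "Transitions from all model states to death will be extracted from age and sex adjusted all-cause mortality statistics from the ONS". In Table 2 the death rows for LTOT, I-WOTCH tapering (IT) and patient-driven tapering (PT) read "All-cause mortality data from ONS", and the row for SOLMP reads "All-cause mortality rates from ONS". No row carries a relative risk, a dose effect or an opioid-specific excess.

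The trial-based equations do not cover death: "Transition probabilities between all the other model states will be derived using risk equations from regression models".

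The text below Figure 1 gives the routes to death: "transitions into the absorbing D state are allowed from the LTOT, IT, PT and SOLMP states". It lets adverse events occur in LTOT, but the only transition it says they may trigger is LTOT to PT. No separate fatal-event route is described.

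On the outcome, the section on health outcomes says: "The CEA will integrate predicted survival and EQ-5D index scores". The time horizon of the cost-effectiveness analysis is the patient's lifetime (Time horizon).

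On motivation, the Background lists "respiratory depression and opioid-related deaths" among the serious harms of opioids, and the Discussion notes that opiates are a frequent cause of drug-poisoning death in the UK. Under Strengths, the model is said to reflect "long-term adverse events associated with both opioid use and opioid withdrawal".

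Under Probabilistic sensitivity analyses, parameter distributions come from the variance-covariance matrices of the regressions. The scenario analyses concern distributional assumptions, with the parametric survival distribution as the example.

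**The concern.** The model's main job is to carry differences in opioid use beyond 12 months. Opioid-related death is one of the harms that the article uses to justify the work. If the death rate does not depend on the state a patient is in, time spent on or off opioids cannot change life expectancy in either direction. The survival part of the incremental QALYs is then set by assumption, without a stated reason.

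What is at stake is less the point estimate than the uncertainty statement. The acceptability curve would be read as covering parameter uncertainty over a lifetime, while one component is held at exactly zero with no variance. A reader of the ICER could not tell whether the conclusion would survive a modest mortality effect.

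**Working it through.** The document gives no survival figure, so there is nothing to reproduce. The check has three parts.

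**1. Structure.** Let q(t) be the death probability in cycle t, common to LTOT, IT, PT and SOLMP. Whatever the movement among these four states,

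alive(t+1) = alive(t) × (1 − q(t)), so S(t) = the product of (1 − q(u)) over all earlier cycles u.

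No engagement, tapering or relapse probability enters. Within any age and sex profile, S(t) is the same in both arms.

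Numerical confirmation used a cohort model with the article's five states and allowed transitions, 17 weekly cycles and then monthly cycles. Mortality was an assumed Gompertz curve standing in for the ONS tables (0.008 per year at age 60, log-slope 0.10 per year). Over 200 random sets of transition probabilities, the largest absolute life-year difference between arms was 5e-14, which is zero to rounding.

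**2. Can the planned uncertainty analyses move it?** The sampled distributions come from regression covariance matrices, and the ONS rates come from no regression. Even if the common rate were sampled, each draw would apply to both arms. Changing a distribution for the trial-based transitions alters movement among living states, which part 1 shows has no effect on S(t). The difference stays at zero in every draw and in every scenario described.

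**3. How large might the omitted term be?** All inputs here are assumptions except the 3.5% rate (Discount rate section): age 60; Gompertz hazard h(60) = 0.006 to 0.008 with slope 0.10 (life expectancy about 22 to 24 years at the ONS-like rate); hazard ratio (HR) for LTOT versus SOLMP of 1.2, 1.5 or 2.0. The quantity is discounted life-years starting in SOLMP minus discounted life-years staying in LTOT.

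| HR | no relapse | 1% monthly return to LTOT | 2% monthly return |
|---|---|---|---|
| 1.2 | 0.67 to 0.70 | 0.17 to 0.20 | 0.08 to 0.10 |
| 1.5 | 1.52 to 1.57 | 0.40 to 0.46 | 0.20 to 0.23 |
| 2.0 | 2.64 to 2.71 | 0.71 to 0.81 | 0.36 to 0.42 |

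At HR 1.0, which is the plan as written, every cell is 0.

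Those figures are per patient moved. For a difference between arms, the cohort model was run with the multiplier on LTOT, IT and PT and none on SOLMP. Assumed inputs were 70% engagement and monthly probabilities IT to SOLMP 3%, IT to LTOT 5%, LTOT to PT 1%, PT to SOLMP 1% and PT to LTOT 10%. The discounted gain per participant at multipliers 1.2, 1.5 and 2.0 was:

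- with 1% monthly return from SOLMP: 0.05, 0.11 and 0.19 life-years;
- with 0.2% monthly return: 0.11, 0.26 and 0.45 life-years.

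**The case against.** Equal mortality is a defensible base case. The target sample is 542 participants followed for 12 months, and nothing suggests that this could estimate mortality by state. The Limitations section accepts that long-term events will be missed. Published opioid mortality ratios are observational, and reading them as causal could import confounding and inflate the QALY gain. If opioids do raise mortality, equal rates work against the intervention and are conservative. This stands, and it is why the base case need not be replaced.

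The article is also condensed. Table 2 lists key parameters, the text allows other public evidence, published sources and expert opinion, and a paper on the model's events and transitions is in preparation. A mortality multiplier could therefore still be added. That limits how much can be read into the missing scenario, but the mortality source is already fixed here for every living state.

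Four stronger readings are tempting and not supported:

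- **That the model is said to represent opioid mortality and fails to.** No section says so. Strengths speaks of long-term adverse events, and non-fatal events can still act through costs and utilities.
- **That equal mortality contradicts the use of predicted survival.** QALYs need a survival curve even when both arms share it.
- **That the 7.5% in the Background is a death rate to put into the model.** It follows a list of several serious adverse events and cannot safely be read that way.
- **That 0.67 to 2.7 life-years is the expected loss.** It assumes a lifelong move to SOLMP, whereas Figure 1 and Table 2 allow return to LTOT.

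**Conclusion.** The point holds as a structural one. Under the stated rule, life-years are identical in both arms for any tapering success or relapse rate, incremental QALYs come only from utility differences, and no analysis described in the article can show otherwise. This follows from the text and needs no assumption beyond applying the same age and sex profile to both arms. Costs and utilities are unaffected.

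The size of what is left out is not derivable from the document and depends strongly on relapse: under the assumptions shown, a 1% monthly return to LTOT cuts the per-patient figure to about 0.2 to 0.8 discounted life-years, roughly a quarter to 0.3 of the no-relapse figure. The defect is an untested and unexplained assumption about a harm cited as motivation. It is not an error in the base case.

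**What to change.** Keep equal ONS mortality as the base case and give the reason for it in a sentence. Pre-specify beside it one scenario in which the ONS rate is multiplied by a state-specific relative mortality for LTOT, for IT and PT, and for SOLMP, taken from published evidence, with its uncertainty sampled in the probabilistic sensitivity analysis. Report life-years, QALYs, the ICER and the acceptability curve under both.

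The cost is a short literature search and up to three further model parameters. Table 2 already draws on published literature for LTOT utility and cost, so the approach is not new to this model. The downside is that the ratios are observational and may be confounded, so the scenario should be labelled as resting on that evidence and should not displace the base case.

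### Table 2 does not follow the rule that trial regressions supply every state's cost and utility: published LTOT values are unranked, SOLMP cost is an assumption, and IT lists only the intervention cost

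*Protocol article*

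**What the plan says.** The text under Populating model parameters in the Protocol article sets a general rule: "Costs and utilities parameters for each of the model states and events will be estimated using the regression models described in the Statistical analysis section". The same paragraph says that initial values will draw on trial patient data, GP records and relevant public evidence.

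Table 2 in that section lists the sources state by state.

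- LTOT utility has two sources: published literature ("Utility of opioid therapy") and the trial questionnaire ("Regression analysis of patient self-reported EQ-5D").
- Utilities for patient-driven tapering (PT), IT and SOLMP have one source each, the trial EQ-5D regression.
- LTOT cost has three sources: published literature ("Cost of opioid therapy per cycle"), then the trial questionnaire and GP records ("Costs associated with self-reported resource use Costs associated with resource use collected").
- PT cost lists usual care, the questionnaire and GP records.
- IT cost lists one item: "Cost associated with intervention".
- SOLMP cost is marked as an assumption from published literature, "1× contact with GP", with no trial source and no period stated.

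Nothing says whether the published LTOT values replace the trial estimates, are pooled with them, or only check them.

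**The concern.** LTOT is where every patient starts and where those who abandon tapering or resume opioids return. The model's gains are therefore contrasts with LTOT. If the LTOT utility or cost came from other patients while the comparison states came from the trial, any difference between sources would be counted as an effect of leaving opioids.

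The cost rows raise a related problem of scope. LTOT and PT carry trial healthcare use, whereas SOLMP carries one assumed contact and IT carries only the programme. A cost difference between states could then reflect what was counted and not what patients used.

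The planned uncertainty analyses would not bring this out. The probabilistic sensitivity analysis (PSA) takes its distributions from regression covariance matrices, and the scenario analyses named with it concern distributional assumptions, not the choice of source.

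**Working it through.** The article gives no state utility, state cost or ICER, so there is no figure to reproduce. The check compares Table 2 with the rule and then asks how an error in the reference state would carry through.

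**Step 1: rows against the rule.** Published literature appears in 1 of 4 utility rows (LTOT) and 2 of 4 cost rows (LTOT, SOLMP). Both LTOT rows also list trial data. The SOLMP cost row lists none. The IT cost row is from the trial but omits healthcare use. The article's own definition of total cost, under Within-trial cost-consequences analysis, adds healthcare items to the cost of the intervention or usual care, so the IT row is narrower than that definition.

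**Step 2: how an LTOT utility error carries through.** Deaths from every living state use the same age- and sex-adjusted all-cause statistics, so discounted life-years are equal between arms. Let ΔT_s be the between-arm difference in discounted time in state s, and ΔT the sum over PT, IT and SOLMP. Then ΔT for LTOT is −ΔT, and, leaving aside separate adverse-event terms,

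ΔQALY = Σ over PT, IT, SOLMP of (u_s − u_LTOT) × ΔT_s.

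If the published LTOT utility differs from the trial value by b and has weight w in the base case, ΔQALY shifts by −w × b × ΔT. Full replacement is w = 1; use as a check only is w = 0.

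**Step 3: illustration.** The documents give neither b nor ΔT; both are assumed here. Sizes with w = 1, valued at £20,000 per QALY:

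- b = 0.02, ΔT = 0.25 years: 0.02 × 0.25 = 0.005 QALY, £100.
- b = 0.05, ΔT = 1 year: 0.05 × 1 = 0.05 QALY, £1,000.
- b = 0.10, ΔT = 2 years: 0.10 × 2 = 0.20 QALY, £4,000.

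To give ΔT some meaning: a 10-percentage-point difference in time outside LTOT, held for 10 years at the article's 3.5% discount rate, gives an annuity of (1 − 1.035^−10)/0.035 = 8.32 and ΔT = 0.10 × 8.32 = 0.83 years. With b = 0.05 the shift is 0.042 QALY, or £832.

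Against an assumed true gain of 0.05 on leaving LTOT, b = 0.02 is 0.02/0.05 = 40% of the gain, and b = 0.05 is all of it.

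**Step 4: costs.** The same algebra applies. An error e in annual LTOT cost shifts incremental cost by −w × e × ΔT; an error e in SOLMP or IT cost shifts it by e × ΔT for that state. The documents give no value for e.

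**Step 5: can the trial supply the LTOT value?** Table 1 collects EQ-5D-5L and questionnaire resource use at baseline, 4, 8 and 12 months, and all participants start in LTOT. With the target of 542, complete data and an assumed SD of 0.20 to 0.35, the SE of mean baseline utility is 0.20/√542 = 0.009 to 0.35/√542 = 0.015. The 95% half-width is 1.96 times that, about 0.017 to 0.03.

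**The case against.** The strongest defence is that the plan does not commit to mixing sources. The trial regression stands in the LTOT utility row, trial resource use stands in the LTOT cost row, and the paragraph that states the rule also admits public evidence. The Strengths and Limitations sections say openly that published data will be used. The published LTOT values may be no more than starting values or checks. All of this stands. A reader might infer that the plan builds a cross-population bias into the ICER; the documents do not support that. The cited sources are not shown, so a different population, instrument or value set cannot be established, and the article sets costing at 2019 prices.

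A second defence is that this is a condensed article, with a fuller account of the model promised elsewhere. Silence on ranking alone could be excused on that ground. A stated rule and a source table that disagree are a different matter, and the SOLMP and IT cost rows are definite entries.

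A third is that 12 months of follow-up cannot inform a lifetime model. The Limitations section makes this argument mainly about long-term events and transition probabilities. It supports outside evidence as a scenario for long-run LTOT, but it does not explain a published value for a state that every participant occupies at baseline.

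Finally, using trial data throughout would not make the contrast between SOLMP and LTOT a randomised one, because patients reach SOLMP through their own response. That is correct. The change removes a difference of source or scope, not confounding.

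**Conclusion.** The point holds as an inconsistency between the stated rule and Table 2. The base-case source for LTOT utility and cost is left open, the SOLMP cost uses no trial data, and the IT cost omits healthcare use. The SOLMP row departs from the rule most plainly.

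The effect on the results is a possibility, of unknown direction and size. Under the assumed gaps and times above it runs from nil (published LTOT values used only as a check) to 0.20 QALY, or £4,000 at £20,000 per QALY (full replacement, largest assumed values). Pooling would fall between, in proportion to the published value's weight. The QALY calculation rests on equal mortality across living states, which the article states, and on assumed values of b and ΔT, which it does not give. It covers the LTOT utility only; the cost rows cannot be sized from the document.

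**What to change.** In the base case, estimate utility and healthcare cost for LTOT, PT, IT and SOLMP from the I-WOTCH EQ-5D and resource-use regressions, and add the intervention cost for IT. Move the published LTOT utility and cost, and the one-GP-contact assumption for SOLMP, to scenario or validation analyses. Correct Table 2 so that each row agrees with the text.

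This changes the table and wording and needs no new data collection. The one downside is that the trial estimates for SOLMP may be imprecise if few participants stop opioids completely. The PSA would then show that imprecision, which an assumed single contact would conceal.

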## Methods

### Study details (population, setting, location, intervention and comparator)

A detailed study protocol for the I-WOTCH trial has been reported in a separate manuscript.^19^ Briefly, I-WOTCH is a multisite, patient-centred, open RCT enrolling adult patients with non-malignant chronic pain in England. The trial’s target sample size is 542 participants, individually randomised (1:1) to receive the I-WOTCH intervention or best usual care. The I-WOTCH intervention is an 8–10 weeks’ course—consisting of a mixture of group sessions led by two trained I-WOTCH facilitators, two one-to-one individual sessions and two telephone consultations with the I-WOTCH-trained nurse facilitator—adjunct to best usual care. Best usual care consists of general practitioner (GP) care with relaxation package and a booklet called ‘My Opioid Manager’.

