### Within-trial cost-consequences analysis

The CCA will focus on estimating and reporting mean health outcomes, resource use and costs by treatment arm at each follow-up interval. No incremental analysis will be conducted. Total costs will be the sum of the costs of the healthcare resource items (described in table 1) that patients used during the study period, plus the cost of either the I-WOTCH intervention or the usual care. Mean health outcomes will include those described in the Identification, measurements and valuation section and be reported at each follow-up period by treatment arm.

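### Table 2 costs the tapering and opioid-free states without the trial resource use that the text promises for every state; if followed, it would tend to favour I-WOTCH

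*Protocol article*

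**What the plan says.** The Markov model has four living states: long-term opioid therapy (LTOT), I-WOTCH tapering (IT), patient-driven tapering (PT) and successful opioid-less management of pain (SOLMP).

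The text sets one rule for costing them. Under Populating model parameters: "Costs and utilities parameters for each of the model states and events will be estimated using the regression models described in the Statistical analysis section". The Modelling section likewise ties each state's average cost and utility to the methods of the Statistical analysis section.

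The cost rows of Table 2, in the same section, list these sources:

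- LTOT: "Cost of opioid therapy per cycle" from published literature, with questionnaire and GP-record resource use.
- PT: "Cost associated with usual care Costs associated with self-reported resource use Costs associated with resource use collected".
- IT: "Cost associated with intervention", and nothing else.
- SOLMP: "Assumption—1× contact with GP", from published unit costs, with no period stated.

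Study details describes the intervention as "adjunct to best usual care". The Figure 1 legend says IT is entered only at the start of the trial and that entry depends on the trial arm.

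**The concern.** Text and table cannot both be followed. One assumed GP contact is not a regression estimate, and an intervention cost is not the full cost of a patient who is still tapering and still receiving usual care.

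The two rows without trial resource use are also the two that matter most for the comparison. Only the intervention arm can occupy IT, and SOLMP is the state that the intervention aims to reach. A cost category counted in LTOT and PT but dropped from IT lowers cost in one arm only. It would also depart from the stated NHS and Personal Social Service perspective, and it would feed directly into the incremental cost and the cost-effectiveness ratio.

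None of the planned analyses named in the article would expose this. The probabilistic sensitivity analysis samples from regression covariance matrices and cannot restore a category that was never included. The scenario analyses named for the model concern distributional assumptions. The one-way or threshold analysis of costing assumptions is stated for the within-trial cost-consequences analysis.

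**Working it through.** **Step 1. Sources side by side (Table 2).**

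| State | Cost: trial resource use listed? | Utility: trial EQ-5D regression listed? |
|---|---|---|
| LTOT | yes | yes |
| PT | yes | yes |
| IT | no | yes |
| SOLMP | no | yes |

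The utility rows show that the table expects patient-level data in all four states. Table 1 collects medication, hospital, GP, nurse, therapy and social-work use from all participants, without restriction by state. So the gap in the cost rows is not explained by data that were never collected.

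**Step 2. Direction.** The article states no state cost, transition probability or cost-effectiveness ratio, so there is no figure to reproduce. Let *b* be the true background cost per month, set equal in every living state so that the true background difference between arms is zero. Let *g* be the monthly cost of the assumed GP contact. Costing as Table 2 reads gives a spurious saving per I-WOTCH patient of

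saving = *b* × (months in IT) + (*b* − *g*) × (extra discounted months in SOLMP under I-WOTCH).

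The first term is positive whenever *b* > 0. The second has the same sign only if the extra SOLMP time is positive and *g* < *b*.

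**Step 3. Illustration.** All values here are assumptions except the cycle structure and the 3.5% discount rate:

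- 70% engage in IT.
- Monthly transitions: IT to SOLMP 6%, IT to LTOT 15%, LTOT to PT 1%, PT to SOLMP 3%, PT to LTOT 20%.
- SOLMP relapse 0.5%, 2% or 5% a month; mortality 1% a year.
- 17 weekly cycles, then monthly, for 35 years; discounting after year 1.
- *g* = £39 a month.

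*IT omission alone.* IT to SOLMP is set to 0 and IT to LTOT to 21%, with relapse 2%. Mean time in IT is 3.15 months and the SOLMP difference is −0.16 months.

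- *b* = £50: 50 × 3.15 − 11 × 0.16 ≈ £156
- *b* = £100: 100 × 3.15 − 61 × 0.16 ≈ £305
- *b* = £200: 200 × 3.15 − 161 × 0.16 ≈ £605 (unrounded months)

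Time in IT drives this. If engaged patients stayed in IT only for the 8–10-week course, mean time would be 0.7 × 8 × 12/52 = 1.29 to 0.7 × 10 × 12/52 = 1.62 months. The omission would then run from 50 × 1.29 ≈ £65 to 200 × 1.62 ≈ £323.

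*IT and SOLMP together.* Mean time in IT is 3.22 months. Extra SOLMP time is 3.56, 7.88 or 19.49 discounted months at relapse of 5%, 2% or 0.5%.

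| *b* per month | relapse 5% | relapse 2% | relapse 0.5% |
|---|---|---|---|
| £50 | £200 | £248 | £376 |
| £100 | £540 | £803 | £1,511 |
| £200 | £1,218 | £1,913 | £3,783 |

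Check of one cell: 100 × 3.22 + 61 × 7.88 = 322 + 481 = £803.

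**Step 4. Where the SOLMP term reverses.** At *b* = £30 and relapse 2%, the sum is 30 × 3.22 − 9 × 7.88 ≈ £26, because the SOLMP term now works against I-WOTCH. The missing period matters too: one contact per weekly cycle would cost 39 × 52/12 = £169 a month while weekly cycles last (the first 4 months).

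**Step 5. Scale.** At £20,000 per QALY, a saving of £156 to £605 is worth 156/20,000 = 0.008 to 605/20,000 = 0.030 QALY. At the £5,000 lower bound that the article also uses, it is worth 0.031 to 0.121 QALY.

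**The case against.** The strongest reply is that the text already prescribes regression-based costs for every state and describes Table 2 as the source of initial values. On that reading the rows for IT and SOLMP are incomplete listings. The table does seem to list candidate sources rather than sums: the LTOT utility row gives both a published value and a trial regression, which cannot be added. Model detail is deferred to a separate paper. The Limitations section also says that some parameters may need published sources or expert opinion, and few patients may be observed in SOLMP.

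Much of this stands. A reader might infer that a false saving is fixed into the design, but the document does not support that: if the text governs, no such bias arises. A reader might also treat the whole SOLMP gap as false. That is not supported either. Patients there take no opioids, and the Modelling section places opioid-related adverse events in LTOT, so some lower cost may be real. SOLMP can also be reached from PT, so only the difference in occupancy between arms counts.

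A third tempting inference is that the within-trial total, "plus the cost of either the I-WOTCH intervention or the usual care", drops usual care from the I-WOTCH arm. That total already counts all Table 1 resource use in both arms. What the wording could leave out is the relaxation CD and booklet, and the cost-consequences analysis makes no incremental comparison. It is not part of this point.

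What the reply does not remove is the conflict itself. The SOLMP row is an explicit assumption, not an abbreviated regression entry. The article defines initial values as a mean, SD or CI and describes no later step that replaces them.

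**Conclusion.** The point holds as a contradiction between the text and Table 2, with a conditional bias. If Table 2 is followed, background cost is missing from IT, a state entered by one arm only, and incremental cost is biased towards I-WOTCH. For SOLMP, the direction is the same only under the two conditions in Step 2, and neither can be settled from the article.

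No size can be derived from the document. On the stated assumptions the IT part is roughly £150 to £600 per patient at £50 to £200 a month, and less if time in IT is limited to the course. The combined figures of about £200 to £3,783 depend further on assumed relapse, SOLMP occupancy and a monthly contact, and they treat none of the lower SOLMP cost as real. They show that the choice can matter, not how large the effect will be.

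**What to change.** Reconcile the Table 2 cost rows with the Modelling and Populating model parameters text before the economic analysis:

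- Cost LTOT, PT, IT and SOLMP from the same regression basis, using questionnaire and GP-record resource use.
- In IT, add the I-WOTCH microcost on top of that resource use.
- Keep the single GP contact for SOLMP only as a scenario, and state the period it covers.

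Any genuine saving in SOLMP, such as no opioid cost, will then appear in the estimate.

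The cost is a wording change in Table 2 and two more state-cost estimates from data already being collected. The downside is precision: few patients may be observed in SOLMP, so its cost will be less certain. The probabilistic sensitivity analysis is the right place to carry that uncertainty.
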